### Randomization, Allocation Concealment Mechanism, and Blinding

Participants will be randomized to the GXST group or placebo group in a 2:1 ratio using the Central Randomization System to achieve computerized randomization in blocks of six, stratified by center. The random sequence will be retained in an envelope and sealed subsequently. According to the randomization number, a statistician will send the envelope directly to Shaanxi Buchang Pharmaceutical Co., Ltd. for labeling of the intervention drug and placebo drug. All researchers, participants, physicians, drug administrators, and dispensing nurses will be blinded to the type of treatment until the study is completed. Unblinding will be available if participants experience an SAE or need to be rescued in an emergency situation. Once unblinded, the participant will withdraw from the study. Researchers should report the reasons to the inspector within 24 h. The precise cause of unblinding, date of the AE, the treatment situation, and the results must be recorded in eCRFs.

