### Criteria for Withdrawal, Removal, Dropout, and Termination

The withdrawal criteria will be 1) exacerbation or deterioration that is clearly related to intake of the study drug; 2) an allergic reaction that is clearly associated with the study drug; 3) comorbidities, complications, adverse events (AEs), or serious adverse events (SAEs) during the trial, such as the necessity of long-term intravenous medication, repeated hospitalization for heart failure, or New York Heart Association (NYHA) class-IV symptoms; 4) the use of forbidden drugs or receipt of prohibited treatment affect the measures of efficacy and safety; 5) poor compliance by participants, or the amount of drug used does not meet the regulations (<80% or >120%); 6) participants request to withdraw from the study; 7) the blinding is uncovered or emergency unblinding is required.

Participants who fail to complete the observational period proposed in the trial, regardless of time and reasons, will be considered to be “dropout” cases. Reasons for dropout will be recorded in electronic case report forms (eCRFs), and the last data recorded will be included in data analyses. During the trial, a participant may be removed if he/she 1) is included mistakenly due to a misdiagnosis, 2) has not taken medication after study inclusion, 3) is participating in other clinical trials, and 4) has incomplete data and no evaluable records after inclusion. Another reason for removal is if the combined use of drugs has a great influence on the efficacy and safety of the study drug. Removal cases will not be included in analyses of the intention-to-treat (ITT) population.

The entire research study will be terminated if 1) there is a poor clinical effect of the test drug, and there is no need to continue the trial; 2) there are major defects in the trial; and 3) administrative authorities terminate the trial.

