### Interventions

Eligible participants will be allocated randomly to the GXST group or placebo group. If GXST have been used before randomized, a 2-week drug washout period should be implemented to avoid any potential complication from GXST. All participants will receive standard treatment.

The GXST group will receive GXST (batch number: 190214, 0.3 g per capsule, op, 3 capsules per time, thrice daily). The placebo group will receive capsule stimulants (batch number: 190215, 0.3 g per capsule, op, 3 capsules per time, thrice daily).

Concerning standard treatment, during the intervention period, according to the guidelines for CHF treatment (Ponikowski et al., 2016; Chinese Society of Cardiology and Chinese Medical Doctor Association, 2018), ACEIs, and/or angiotensin receptor blockers, β-blockers, aldosterone receptor blockers, or diuretics should be used. TCM formulations with a similar composition and efficacy to those of GXST will not be allowed to be used. Concomitant treatments for comorbidities (e.g., hypertension, diabetes mellitus, hyperlipidemia, and other chronic conditions) are permitted during the intervention. Researchers should record the concomitant medication truthfully and maintain dose stability during the trial.

Concerning emergency treatment, in the event of an SAE or acute exacerbation of the disease during treatment (e.g., acute heart failure and acute coronary syndrome), participants should be treated first, and the treatment status should be recorded as an AE record form and combined medication record form. If the participant's condition deteriorates during treatment and it is not advisable to continue the trial (e.g., long-term intravenous medication, repeated heart failure that necessitates hospital admission, or NYHA class-IV symptoms), one should consider terminating the trial and switching to surgery or another type of clinical treatment. Patients will be classified in the analysis as “treatment ineffective.”

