The secondary outcomes are 1) changes in plasma levels of N-terminal pro-B-type natriuretic peptide (NT-proBNP) (Booth et al., 2014; Roberts et al., 2015). NT-proBNP will be detected centrally by Zhejiang Chinese Medical University using a standard kit and fixed operating procedures; 2) improvement in NYHA functional class (The Criteria Committee of the New York Heart Association, 1994); 3) improvement in the Minnesota Living with Heart Failure Questionnaire score (Rector and Cohn, 1992); 4) improvement in echocardiographic measurements of left ventricular end-diastolic diameter and LVEF; 5) the incidence rate of clinical endpoint events (rehospitalization for acute aggravation of CHF, cardiogenic death, and all-cause death).

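### Unblinding, worsening heart failure and poor adherence are treated as withdrawal from the study, which conflicts with the plan's 52-week event follow-up, log-rank test and ITT statement

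*Protocol article*

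**What the plan says.** **Leaving the study.** The section on randomization, allocation concealment and blinding sets the trigger ("Unblinding will be available if participants experience an SAE or need to be rescued in an emergency situation") and the consequence ("Once unblinded, the participant will withdraw from the study"). The section on withdrawal, removal, dropout and termination gives seven withdrawal criteria. Item 3 covers comorbidities, complications and adverse events, "such as the necessity of long-term intravenous medication, repeated hospitalization for heart failure, or New York Heart Association (NYHA) class-IV symptoms". Item 4 is prohibited treatment that affects the measurements, item 5 is drug use below 80% or above 120%, item 6 is the participant's own request to leave, and item 7 is that "the blinding is uncovered or emergency unblinding is required". Anyone who does not complete observation, for any reason, is a dropout, for whom "the last data recorded will be included in data analyses". A separate removal rule takes participants out of the ITT population, among other reasons for influential concomitant drugs.

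**What is to be observed.** The clinical endpoint events are "rehospitalization for acute aggravation of CHF, cardiogenic death, and all-cause death". Table 5 collects them every 4 weeks until week 52, and Table 6 compares them by log-rank test. Table 5 schedules 6MWD, the primary outcome, at baseline and week 12 only. The Statistical Analyses section invokes ITT and fills missing values by last observation carried forward (LOCF). The Trial Completion section ends the trial when every patient has completed 52 weeks.

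**The concern.** The article does not separate stopping study drug from leaving the study. Several reasons for leaving are components of the event endpoint or plausible predictors of it. Ending observation for those reasons means that the follow-up lost is disproportionately that of patients who are doing badly. A log-rank comparison assumes that censored patients have the same outlook as those still observed at that time, and these rules work against that assumption.

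The primary outcome is affected by a different route. With no 6MWD between baseline and week 12, the last value for anyone withdrawn in between is the baseline walk, so the change is recorded as exactly zero. A participant who deteriorated is scored as unchanged, although some could still have walked at week 12. Outcomes not collected at the time may not be recoverable, and the article reports that recruitment is under way.

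**Working it through.** **1. Do the rules mean leaving the study, or only stopping drug?** Item 6 of the withdrawal list is about leaving the study. Item 7 (unblinding) is given the same meaning, without condition, in the blinding section. Items 3, 4 and 5 stand in the same list under the same heading. The dropout sentence then uses the last recorded data, which implies that collection has stopped. No section provides for follow-up afterwards. The text therefore reads as leaving the study.

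**2. Which endpoints are exposed?**
- *Time to first event, if a composite:* a patient withdrawn for repeated heart failure admission has normally already had an event and is counted. Patients withdrawn for NYHA IV, unblinding or non-adherence may not have had one, so a later first event is lost.
- *Cardiogenic and all-cause death:* every trigger can precede the death, so deaths after withdrawal are lost.
- *6MWD:* affected only by withdrawal before week 12.

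**3. The plan's own sample size.** With δ = 30 m, σ = 100 m, k = 2, one-sided α = 0.025 and power 80%: n₁ = [(1.960 + 0.842) × 100/30]² × 1.5 = 130.8. The total is 3 × 130.8 = 392.4, and 392.4 × 1.2 = 470.9, which matches the stated 470. The inputs below are therefore the plan's own.

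**4. 6MWD power (assumed share d carried forward at 0 m, equal in both arms).** For 320 versus 160, SE = 100 × √(1/320 + 1/160) = 9.68 m. With complete data, power = Φ(30/9.68 − 1.96) = 87.3%. With share d at zero, the difference becomes 30(1 − d).

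| d | Difference | Power, SD held at 100 m | Power, SD narrowed by the zeros |
|---|---|---|---|
| 5% | 28.5 m | 83.7% | 85.5% |
| 10% | 27.0 m | 79.6% | 83.5% |
| 20% | 24.0 m | 69.8% | 78.9% |

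The last column takes a placebo mean change of 0. The variance is (1 − d) × 100² in the placebo arm and (1 − d) × 100² + d(1 − d) × 30² in the GXST arm. At d = 20%: SE = √(8144/320 + 8000/160) = 8.69 m, and Φ(24/8.69 − 1.96) = 78.9%. Excluding the same 20% instead would give 79.1%.

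*Bias from unequal withdrawal:* if withdrawn patients truly lose 50-100 m, each 5-point difference between arms shifts the estimate by 0.05 × 50 = 2.5 m to 0.05 × 100 = 5 m, in favour of the arm with more withdrawals.

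**5. Deaths (all rates assumed).** Take a death hazard h = 0.05 per year while stable. Withdrawal for worsening is w = 5-15% by week 52, at rate λ = −ln(1 − w). The hazard afterwards is r × h with r = 3-10.
- Deaths seen = h/(h + λ) × (1 − e^−(h+λ)).
- All deaths = 1 − e^−(h+λ) − λ × (e^−(h+λ) − e^−rh)/(rh − h − λ).
- w = 5%, r = 3: seen 0.0476, all 0.0511, so 93% are seen. In 480 patients, about 1.7 of 24.5 deaths are missed.
- w = 15%, r = 10: seen 0.0450, all 0.0773, so 58% are seen. In 480 patients, about 15.5 of 37.1 deaths are missed.
- With censoring at withdrawal, Kaplan-Meier mortality at 52 weeks reads 1 − e^−0.05 = 4.9%, against a true 5.1% to 7.7%.

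**The case against.** Much can be said for the plan. The heart failure trigger is *repeated* hospitalisation, so a first admission is counted and the patient stays in. Unblinding after an SAE is available, not required. The Interventions section only asks that termination be considered when a patient deteriorates. Early withdrawals stay in the primary analysis through LOCF, and the triggering event is recorded. Table 6 compares adherence below and above 80%, so some data on poor adherers are expected. The event endpoint is secondary and the trial is not sized on it. A condensed article may also leave follow-up off drug to the full protocol.

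These points limit the concern. A reader might infer any of the following, and the documents support none of them:
- *Every SAE ends participation, or deaths after a first heart failure event go uncounted.* The wording of the triggers is narrower than that.
- *Early withdrawals vanish from the primary analysis.* They are kept, at 0 m.
- *The rules cause much of the 20% dropout.* The Sample Size section gives 20% only as a possible rate, with no reasons.
- *A third to a half of deaths are lost.* That needs 15% withdrawn (72 of 480), all with a 15-30% later death risk, against 5% in the other 408: 10.8/31.2 = 35% and 21.6/42.0 = 51%. It puts excess mortality on poor adherers and users of prohibited drugs, for which the article gives no basis.
- *The bias favours GXST.* Direction depends on withdrawal by arm, which is unknown. If withdrawal and prognosis are alike in both arms, the log-rank test keeps its level under no effect.

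What does not stand is the appeal to condensation. The article affirmatively states that an unblinded participant leaves the study. That is a stated rule in conflict with other stated rules, not an omitted detail.

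**Conclusion.** The point holds. As written, the withdrawal rules end observation for reasons tied to prognosis, and they cannot be reconciled with event collection to week 52, the log-rank comparison, the ITT statement or completion of 52 weeks by all patients. The main damage is to the death endpoints, and to first events after withdrawal for NYHA IV, unblinding or non-adherence. For 6MWD, early withdrawals enter as unchanged. The label of ineffective treatment in the Interventions section does not help, because it maps onto neither a continuous change nor a time-to-event analysis.

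The size cannot be derived from the documents. The 7-42% of deaths unobserved rests on the assumed 5% annual hazard, 5-15% withdrawn and a 3-10-fold later hazard. The power range of 84-70% assumes that the SD stays at 100 m and is the pessimistic end; letting the zeros narrow the spread gives 85-79%. Both are measured against an ideal of complete data with the full 30 m effect. Walks measured off drug might also show a diluted effect, so the fix may not restore all of that power. Its gain is that deteriorating patients are no longer scored as unchanged.

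**What to change.** Reconcile the sections on withdrawal, blinding and interventions with Table 5, Trial Completion and Statistical Analyses. Suggested wording:

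*Stopping study drug or unblinding does not end study follow-up. All randomised participants who have not withdrawn consent to follow-up keep the scheduled visits, have 6MWD at week 12 where able, and are followed every 4 weeks to week 52 for heart failure hospitalisation and vital status.*

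In addition:
- Censor event analyses only at withdrawal of consent, loss of contact or week 52. Treat deaths that are not part of the endpoint as competing events; this matters for heart failure rehospitalisation and cardiogenic death.
- Let adherence and prohibited medication decide membership of the per-protocol set only. Amend the removal rule to match, since it now takes participants with influential concomitant drugs out of the ITT population.

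The reasons for stopping study drug are left as they are; no view is taken on them. How to score participants who die or cannot walk at week 12 still has to be settled in the analysis plan.

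The cost is an amendment to wording and a small added burden of following patients who are off drug, through visits and 4-weekly contacts already planned. Because recruitment has started, it should be done promptly.

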### Interventions

Eligible participants will be allocated randomly to the GXST group or placebo group. If GXST have been used before randomized, a 2-week drug washout period should be implemented to avoid any potential complication from GXST. All participants will receive standard treatment.

The GXST group will receive GXST (batch number: 190214, 0.3 g per capsule, op, 3 capsules per time, thrice daily). The placebo group will receive capsule stimulants (batch number: 190215, 0.3 g per capsule, op, 3 capsules per time, thrice daily).

Concerning standard treatment, during the intervention period, according to the guidelines for CHF treatment (Ponikowski et al., 2016; Chinese Society of Cardiology and Chinese Medical Doctor Association, 2018), ACEIs, and/or angiotensin receptor blockers, β-blockers, aldosterone receptor blockers, or diuretics should be used. TCM formulations with a similar composition and efficacy to those of GXST will not be allowed to be used. Concomitant treatments for comorbidities (e.g., hypertension, diabetes mellitus, hyperlipidemia, and other chronic conditions) are permitted during the intervention. Researchers should record the concomitant medication truthfully and maintain dose stability during the trial.

Concerning emergency treatment, in the event of an SAE or acute exacerbation of the disease during treatment (e.g., acute heart failure and acute coronary syndrome), participants should be treated first, and the treatment status should be recorded as an AE record form and combined medication record form. If the participant's condition deteriorates during treatment and it is not advisable to continue the trial (e.g., long-term intravenous medication, repeated heart failure that necessitates hospital admission, or NYHA class-IV symptoms), one should consider terminating the trial and switching to surgery or another type of clinical treatment. Patients will be classified in the analysis as “treatment ineffective.”

GXST and capsule simulants will be provided by Shaanxi Buchang Pharmaceutical Co. Ltd. The quality control of GXST is important. The method of determination of GXST components is based on the general principles of the 2018 edition of the *Chinese Pharmacopoeia*. Using gas chromatography (General Principle 0521), each GXST capsule should contain eugenol ≥2.0 mg and borneol ≥14.0 mg, and the total amount of borneol and isoborneol should be 25.5–34.5 mg. Using liquid chromatography (General Principle 0512), each GXST capsule should contain tanshinone II-A ≥0.15 mg and salvianolic acid B ≥2.9 mg. The primary content of capsule simulants is corn starch, silica, caramel (liquid), and sunset yellow. We have added 2% GXST powder to the capsule simulants to achieve smell, color, taste, and texture comparable with that of GXST. After treatment, the package will be returned to the researchers.

## Outcomes

### Primary and Secondary Outcomes

The details of items to be measured and the time window of data collection are shown in Table 5. The primary outcome is the improvement in 6-min walk distance (6MWD) (Holland et al., 2014). 6MWD will be measured within 24 h after enrollment and 12 weeks after treatment to evaluate the change in exercise tolerance. Improvement will be calculated using the following formula:

**TABLE 5 T5:** Study schedule.

Study phase time	Baseline period	Intervention period			Follow-up
	Visit 1	Visit 2	Visit 3	Visit 4	Every 4 weeks
	−7 to 0 days	4 weeks	8 weeks	12 weeks	Until 52 weeks
Data collection at baseline					
Informed consent	×				
Inclusion/exclusion criteria	×				
Demographic data	×				
Obtain the central random number	×				
Previous history, medical history, and allergies	×				
Comorbidities and co-medications	×				
Safety evaluation					
Vital signs	×	×	×	×	
Physical examination	×	×	×	×	
Blood routine	×			×	
Urine routine	×			×	
Blood biochemistry	×			×	
Myocardial zymogram and troponin	×			×	
ECG	×			×	
Chest radiograph or CT	×			×	
Urine pregnancy test	×			×	
Efficiency evaluation					
6MWD	×			×	
NT-proBNP	×			×	
NYHA class	×	×	×	×	
MLHFQscore	×	×	×	×	
Echocardiographic parameters	×			×	
Clinical-endpoint events		×	×	×	×
Other work					
Dispense drug	×	×	×		
Recovery and record of study drug		×	×	×	
Metabolomics and proteomics	×			×	
Record AEs		×	×	×	×
Complications due to medications		×	×	×	
Evaluate compliance		×	×	×	×

CT, computed tomography; 6MWD, 6-min walk distance; NYHA, New York Heart Association; MLHFQ, Minnesota Living with Heart Failure Questionnaire; TCM, traditional Chinese medicine; AE, adverse event.

Improvement in exercise tolerance = 6MWD value after treatment − 6MWD value before treatment

The secondary outcomes are 1) changes in plasma levels of N-terminal pro-B-type natriuretic peptide (NT-proBNP) (Booth et al., 2014; Roberts et al., 2015). NT-proBNP will be detected centrally by Zhejiang Chinese Medical University using a standard kit and fixed operating procedures; 2) improvement in NYHA functional class (The Criteria Committee of the New York Heart Association, 1994); 3) improvement in the Minnesota Living with Heart Failure Questionnaire score (Rector and Cohn, 1992); 4) improvement in echocardiographic measurements of left ventricular end-diastolic diameter and LVEF; 5) the incidence rate of clinical endpoint events (rehospitalization for acute aggravation of CHF, cardiogenic death, and all-cause death).

### Safety Outcomes

Safety outcomes comprise vital signs (body temperature, heart rate, breathing, and blood pressure), imaging (radiographs or computed tomography), laboratory examinations (routine blood test, routine urinalysis, serum biochemistry, myocardial zymogram, and troponin test), and AEs (which will be recorded throughout the trial).

### Metabolomics and Proteomics Analyses

Fifty participants per group will be selected randomly for metabolomics and proteomics analyses to explore the biomarkers of GXST for treating CHF.

Metabolomics analyses will be on blood and urine samples. Gas chromatography–mass spectrometry and liquid chromatography–mass spectrometry will be used to detect chemical and biological “fingerprints,” describe the possible metabolic pathways, and identify biomarkers of GXST for CHF treatment.

Proteomics analyses will be of blood samples. Two-dimensional difference gel electrophoresis will be used to establish the proteome of each group before and after the intervention. Matrix-assisted laser desorption/ionization time-of-flight/time-of-flight mass spectrometry will be applied to identify differentially expressed proteins. Bioinformatic analyses are used to assess the biological functions of differentially expressed proteins. The Search Tool for the Retrieval of Interacting Genes/Proteins database and Ingenuity Pathway Analysis (IPA) are employed to establish a protein network affected by GXST.

Concerning the collection of blood samples, participants will fast for 10 h before each collection. Then, 5 ml of blood will be drawn and centrifuged, and serum stored in Eppendorf™ tubes at −70°C. Concerning the collection of urine samples, participants will fast for 10 h before taking the medication (and be allowed to drink water). They will fast, and water consumption will be prohibited 1 h before urine collection to 2 h after taking the medication. Water will be rationed to 200 ml/h for 2–8 h after taking the medication, and a low-fat meal can be consumed 4 h after taking the medication. Urine samples will be collected at baseline and after treatment (28 days) and stored in Eppendorf tubes at −70°C.

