## Methods and Analyses

### Design and Settings

This study is a multicenter, prospective, randomized, double-blind, placebo-controlled, superiority trial. The trial will be conducted by 11 centers throughout China (Table 2), and a total of 480 participants will be recruited. After the participants have been enrolled and provided written informed consent, they will be assigned randomly to the GXST group or placebo group in a 2:1 ratio. This trial consists of a 1-week baseline period, a 12-week intervention period, and a 40-week follow-up period. A flow diagram of the study procedures is illustrated in Figure 1. Participants will be monitored and assessed by the investigators at each study visit. The design follows the rules for Standard Protocol Items Recommendations for Interventional Trials (Chan et al., 2013) and Consolidated Standards of Reporting Trials (CONSORT) (Schulz et al., 2010).

**TABLE 2 T2:** Research setting.

Second Affiliated Hospital of Zhejiang Chinese Medical University
The Affiliated Hospital of Hangzhou Normal University
Pingdingshan First People’s Hospital
Hangzhou First People's Hospital
Fenyang Hospital of Shanxi Province
The Affiliated Hospital of Liaoning University of Traditional Chinese Medicine
Tongxiang Traditional Chinese Medicine Hospital
Shaoxing People's Hospital
Pizhou Traditional Chinese Medicine Hospital
Lishui Central Hospital
First Affiliated Hospital of Xinxiang Medical University

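### The text times the post-treatment urine sample for metabolomics at 28 days, which does not agree with the 12-week treatment period or with the only post-baseline omics visit in Table 5 (week 12)

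*Protocol article*

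**What the plan says.** Four statements in the protocol article bear on when the urine is taken.

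- **Urine time in the text.** The section Metabolomics and Proteomics Analyses says: "Urine samples will be collected at baseline and after treatment (28 days". It does not say what the 28 days are counted from.
- **Trial periods.** Design and Settings gives "a 1-week baseline period, a 12-week intervention period, and a 40-week follow-up period". The abstract and the limitations paragraph of the Discussion also give 12 weeks of treatment.
- **Schedule.** In Table 5 (Primary and Secondary Outcomes) the row "Metabolomics and proteomics" is marked at Visit 1 and at Visit 4 (12 weeks). It is empty at Visit 2 (4 weeks), at Visit 3 (8 weeks) and in follow-up. It is a single row, not divided into blood and urine.
- **Sample types.** "Metabolomics analyses will be on blood and urine samples", while proteomics uses blood only. For proteomics the stated purpose is to "establish the proteome of each group before and after the intervention".

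The text gives no day or week for the blood sample. It gives only a fasting rule: "Concerning the collection of blood samples, participants will fast for 10 h before each collection".

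**The concern.** A before-and-after biomarker comparison needs a defined second time point. Here the text and the schedule give different ones for urine, and the label that the text uses, after treatment, does not describe day 28 of an 84-day course.

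If the text is applied as written and the days are counted from the start, the second urine sample shows an early on-treatment state, not the state at the end of the course. It is then also taken at a different visit from the one that Table 5 gives for omics sampling. Urine and blood metabolomics would describe different stages of treatment while carrying the same label. At stake is the interpretation of the urine metabolomics only.

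**Working it through.** **Inputs**

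- Urine time in the text: 28 days (Metabolomics and Proteomics Analyses).
- Treatment length: 12 weeks (Design and Settings).
- Omics visits: Visit 1 (−7 to 0 days) and Visit 4 (12 weeks) (Table 5).
- Substudy size: 50 participants per group (Metabolomics and Proteomics Analyses).

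**Step 1. Can the 28 days be reproduced from the design?**

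Treatment length in days = 12 × 7 = 84. An end-of-treatment sample therefore falls on day 84. The stated 28 days is not reproduced.

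**Step 2. Reading A: 28 days from the start of treatment.**

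- 28 / 7 = 4, so week 4, which is Visit 2.
- Share of treatment completed = 28 / 84 = 0.333, or 33%.
- Distance from the scheduled omics visit = 84 − 28 = 56 days.
- Table 5 has no omics mark at Visit 2, and study drug is still dispensed at Visits 2 and 3, so this time is not after treatment.

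**Step 3. Reading B: 28 days from the end of treatment.**

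- 84 + 28 = 112 days, and 112 / 7 = 16, so week 16.
- This lies in follow-up, where Table 5 has no omics mark.

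**Step 4. Which reading is likelier?**

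The urine procedure is timed around a dose: "participants will fast for 10 h before taking the medication (and be allowed to drink water". That favours Reading A, because study treatment has stopped by week 16. It does not settle the matter, since the medication is not named.

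**Step 5. The places side by side**

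| Source | Post-baseline time | Omics mark in Table 5? |
|---|---|---|
| Text, Reading A | Week 4 (day 28) | No |
| Text, Reading B | Week 16 (day 112) | No |
| Table 5 | Week 12 (day 84) | Yes |

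No reading of the text agrees with the schedule.

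**Step 6. Reach**

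At most 2 × 50 = 100 participants have urine metabolomics, out of 480 randomized (100 / 480 = 21%). This is an upper bound: it applies only if every urine sample follows the text.

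**The case against.** The strongest reply is that this may be a drafting slip in one parenthesis of a condensed article. Centres would work from the full protocol, which is not shown and may give a single consistent time. The substudy is exploratory: omics is not among the primary or secondary outcomes and has no row in Table 6. This stands as a limit on importance. It does not remove the contradiction, because both statements are in the current text and nothing in the article resolves them.

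A reader might also be tempted to infer more than the article supports.

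- **That urine is in fact taken a third of the way through treatment and does not match the blood.** This follows only if the text overrides Table 5 and the days run from the start of treatment. The article settles neither. The text gives no day for blood, so any mismatch with blood is inferred from the undivided row in Table 5.
- **That the link between metabolic change and clinical response is lost.** The article plans no analysis relating urine profiles to 6-min walk distance, NT-proBNP or echocardiography. The stated aim is to look for biomarkers and pathways.
- **That sampling time is confounded with centre.** Nothing shows that the 11 centres follow different instructions. Randomization is stratified by centre, so both arms are recruited within each one. Differing times would mainly add variation and would not by themselves bias GXST against placebo.
- **That samples have been irrecoverably lost.** No statement in the article shows that any urine was taken at the wrong time.

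**Conclusion.** The point holds as an inconsistency between text and schedule. The 28 days in the text agrees neither with a 12-week treatment period nor with the single post-baseline omics visit in Table 5. The discrepancy is 56 days early if counted from the start of treatment (week 4, 33% of the course), or 28 days late if counted from its end (week 16).

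The consequence is conditional: if the text is followed, the sample is not an end-of-treatment sample and is not taken at the omics visit. The article does not show which instruction is being followed.

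The reach is urine metabolomics in an exploratory substudy, at most 50 participants per group. Proteomics and blood metabolomics, the primary outcome at week 12 and the sample size are not affected. Correction is still worthwhile, because a stated sampling rule would give the wrong time if applied and putting it right costs little.

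**What to change.** Reconcile the text with Table 5 and state one post-treatment urine time, by visit and week, for all centres. Visit 4 (week 12) is the natural candidate. It is the only post-baseline omics visit in Table 5, it coincides with the end of treatment, and it fits the before-and-after design stated for proteomics. If an early on-treatment sample was intended, Table 5 should show it as a separate urine row and the text should not call it post-treatment.

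Record the actual collection date of every urine sample. Analyse urine already taken at another time separately, by that actual time, and do not pool it with the end-of-treatment samples.

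The cost is one amended line and a note to the centres. The note should name the visit, because the fasting rule begins before the dose and participants must be prepared in advance. The downside is a smaller main urine set if some samples were taken at another time. Nothing changes in the primary analysis or the sample size.
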